**GF staff**			
**Weekly meeting** (1h) with project coordinators.	Yes	Yes	Yes
**3 training** (4h/training): face to face training with all GF staff that coordinate and implement the project.	Yes	Yes	Yes
**Voice message report** after each family workshop.	Yes	Yes	Yes
**Ongoing support** with project coordinators to tackle all the project needs.	Yes	Yes	Yes

**Fig. 1 Fig1:**
[figure not shown]
FIVALIN High intensity intervention group modality

**Fig. 2 Fig2:**
[figure not shown]
FIVALIN Low intensity intervention group modality

**Fig. 3 Fig3:**
[figure not shown]
FIVALIN control group modality

The project uses theoretical models based on social cognitive theory, such as: i) ASE (Attitude, Social influence, and Efficacy) model [36]; ii) Transtheoretical model [37]; and iii) Motivational interviewing (MI) [38]. Furthermore, the study will also use the Resiliency Theory [39] (see Additionalfile2). Finally, we will implement a multiple behavioral approach that considers dietary habits, PA and sport, screen time, sleep duration and quality, and psychological wellbeing, among children and their parents.

Healthy lifestyles will be implemented by using a pedagogical metaphor for the determinants of childhood obesity, *the Healthy Galaxy* [40]. The metaphor is based on a fantastic recent human story, where healthy habits decided to take off from planet Earth for a new Healthy Galaxy, where they created 4 planets: PA, healthy eating, sleep quality and duration, and emotional wellbeing (see Figs.4, 5 and 6). This story will motivate and promote families participation, while relating all the activities to one aim: families must return the healthy habits to the earth by travelling to the *Healthy Galaxy*. They will go around the galaxy on a spacecraft called FIVALIN and, back on the planet Earth, they will have another mission: spread the word about everything they learned.

**Fig. 4 Fig4:**
[figure not shown]
The Healthy Galaxy characters

**Fig. 5 Fig5:**
[figure not shown]
The Healthy Galaxy Communication material. Poster and Flyer example

**Fig. 6 Fig6:**
[figure not shown]
Educational material included in family activities

A FIVALIN causal pathway was created based on I-Change Model [41] (an integration of ASE model and Transtheoretical model) to clarify the logical framework that relates the intervention, behavioral mechanisms, behaviors, and weight status (*see* Fig.7).

**Fig. 7 Fig7:**
[figure not shown]
FIVALIN causal pathway

The following strategies will be applied to promote adherence and prevent attrition during the project planification and implementation: i) carry out a qualitative session in each participant CCC and community before starting the intervention; ii) facilitate the logistics for attending the workshops by choosing CCC located in the families own communities and providing a childcare service for children under 5years; iii) implement participative and respectful activities during the family workshops, to highlight each positive lifestyle behavior, independently of the cultural background, helping to generates a positive family attachment; iv) deploy a process evaluation protocol to identify areas for improvement, considering families, educators, and CCC opinions; v) consider various individual strategies based on the Motivational Interviewing principles directly addressed to parents (making individual follow up calls, using incentives, sending mobile messages to recall and thanks their participation in the project family workshops).

In conclusion, the plan consists of a multicomponent intervention with strategies at different levels (childrens education, families, and centers organization), that include several activities.

### Data collection

#### Anthropometric variables

Weight will be recorded to the nearest 100g using an electronic scale (SECA 899), and height will be recorded to the nearest 1mm (without shoes) using a portable SECA 213 stadiometer. Waist circumference will be assessed in the narrowest zone between the lowest rib and iliac crest, in the vertical position, with a flexible non-stretch tape measure (SECA 201). Every device is systematically calibrated and all measurements will be performed by a GF-trained researcher.

#### Online questionnaires

All lifestyle data will be reported using online questionnaires. Parents will report information on screen time, diet, sleep duration and quality, and psychological wellbeing of their children. They will also take a questionnaire on their own lifestyles and sociodemographic characteristics. Children will complete a self-assessment questionnaire on PA and physical condition, with the help of GF researchers and CCC educators.

#### The online questionnaires

A.**Data collection for Children**Diet Quality (KIDMED questionnaire)Physical Activity (Physical Activity Unit- 7 Items - PAU-7S)Physical Condition (The international Fitness Scale - IFIS)Screen time-based and Sedentary Behavior (Screen time-based sedentary behaviour questionnaire - SSBQ)Sleep Hours (Sleep-Habits Survey for Adolescents questionnaire - SHSA)Sleep Quality (Bedtime Issues, Excessive Daytime Sleepiness, Night Awakenings, Regularity and Duration of Sleep and Snoring questionnaire - BEARS)Behavior (Strengths and Difficulties Questionnaire - SDQ)

##### Diet quality

Diet quality will be evaluated using the KIDMED index [42], which is based on 16 items with a dichotomous (yes/no) response format, reported by parents. The KIDMED test was created to estimate adherence to the Mediterranean diet in children and young adults. It is based on principles that are aligned or not with the Mediterranean dietary pattern. The index ranges from 4 to 12 and is based on a 16-question test. Answers indicating a negative or positive behavior with respect to the Mediterranean diet are assigned a value of 1 or+1, respectively. The sums of these values are classified into three levels: i)>8, optimal Mediterranean diet; ii) 47, improvement needed to adjust intake to Mediterranean patterns; iii)<3, poor diet quality.

##### Physical activity

Level of PA will be evaluated by using the Physical Activity Unified-7 item Screener (PAU-7S) (see Additionalfile3), which is self-reported by the child (validity results sent for publication and currently under review). The PAU-7S consists of 7 questions referring to the week before the test. Questions 13 address different types of PA, such as walking, team sports, and individual activity, respectively. Questions 46 address the context where the PA was practiced: schoolyard, after school and on weekends, and physical education classes, respectively. The last question refers to whether the child was ill during the previous week or was unable to perform PA for some reason. Questions 16 will be answered according to 5 possible options that refer to time spent (no activity=0min, <30min, 3060min, 6090min, and>90min). The questionnaire will give the total amount of minutes dedicated to PA during the week before the test.

##### Physical condition

Childrens physical condition will be assessed using the International Fitness Scale (IFIS) self-rating questionnaire [43]. IFIS is composed of five Likert-scale questions on childrens shape, in comparison to that of their friends. Children will evaluate their own overall physical condition, cardiorespiratory fitness (CRF), muscular fitness (MF), speedagility (SPAG), and flexibility. They will rank themselves as very poor, poor, average, good or very good. The appraisal of a good/very good overall physical condition, CRF, or SPAG indicates a healthy cardiovascular profile.

##### Screen time and sedentary behavior

Sedentary behaviors will be assessed using the Screen-Time-based Sedentary Behavior Questionnaire (SSBQ) [44], which is reported by parents. 6 questions inquire about behaviors such as: i) watching TV; ii) playing computer games; iii) playing console (video) games; iv) using internet for non-study reasons (hobbies); v) using for study reasons; and vi) studying (outside the school schedule). Parents will separately answer the 6 questions for weekdays and weekends, and will indicate the usual time devoted to the 6 habits: 0min; <30min; 3060min; 60120min; 120180min; 180240min; and>240min. The number of sedentary minutes per day will be rated according to the following categories: 1=0min, 2=15min, 3=45min, 4=90min, 5=150min, 6=210min, and 7=241min, respectively. Weekly sedentary time is calculated by taking the mean time in the selected category and applying this formula: [(weekdays*5)+(weekend days*2)]/7. The total sedentary score is obtained by summing the time reported in each category. Higher scores indicate higher levels of screen time and sedentary behavior.

##### Sleep duration and quality

Sleep patterns will be assessed using the BEARS Questionnaire [45], which will be completed by parents to evaluate potential sleep problems in children. We will consider 5 major sleep domains, such as: B=Bedtime issues; E=Excessive daytime sleepiness; A=night Awakenings; R=Regularity and duration of sleep; and S=Snoring. Parents will give a yes or no response for each domain.

Parents will also complete a Sleep-Habits Survey for Adolescents (SHSA) [46], which will serve to estimate childrens sleep duration. 4 questions will inquire about usual sleeping and waking behaviors. Parents will report the time their children go to bed and wake up during school days and at weekends.

##### Psychological wellbeing

For behavioral screening, the Strengths and Difficulties Questionnaire (SDQ) [47], a brief questionnaire for 3- to 16-year-old children, will be completed by parents. The SDQ collects data on 25 attributes: 5 scales including 5 items each. The scales consist in: i) emotional symptoms; ii) conduct problems; iii) hyperactivity/ inattention; iv) peer relationship issues; and v) prosocial behavior. Parents have three possible choices for each item on these scales: Not True, Somewhat True, and Certainly True. For all scales, higher scores indicate more problems, except for the last scale, where higher scores correspond to fewer difficulties in prosocial behavior. In addition, children will answer a brief self-report question on their own health.

##### Other data collected

We will collect data on birth weight and breastfeeding using a standard questionnaire to be completed by the adults.
B.**Data collection for Parents**Diet Quality (short Diet Quality Screener - sDQS)Physical Activity (REGICOR Short Physical Activity Questionnaire)Sleep DurationPerceived Stress (Perceived Stress Scale - PSS)

##### Diet quality

Diet quality will be analyzed by using a self-report questionnaire: the short Diet Quality Screener (sDQS) [48]. Parents will be asked to base their responses on their dietary behaviors over the previous 12months, reporting their usual intake of 18 food items, grouped in 3 categories. These categories are based on recommended frequencies of food intake. Consumption frequency will be rated 1, 2, or 3 for healthy food items, and 3, 2, 1 for the unhealthy food items. All scores will be added up. Outcomes will range from 18 (low quality diet) to 54 (high quality diet).

##### Physical activity

PA will be assessed by using a self-report REGICOR [49] questionnaire on exercise type, frequency (days per month), and duration (minutes per day). The questionnaire also provides categorical information about PA at work or in everyday life and gives a weekly total amount of training minutes.

##### Sleep duration

Parents sleep duration will be calculated by asking about their usual sleeping and waking times on weekdays and weekends.

##### Perceived stress

The Perceived Stress Scale (PSS) [47] will be used to measure the perception of stress. This self-report questionnaire includes several direct queries about current levels of stress experienced. Questions refer to feelings and thoughts during the previous month. The complete version of the test contains 14 questions with 5 response categories each (0=never, 1=almost never, 2=occasionally, 3=often, 4=very often). PSS scores are obtained by reversing responses (e.g., 0=4, 1=3, 2=2, 3=1, and 4=0) to 4 positively stated questions (4, 5, 7, and 8), and then summing the values. Scores of 013, 1426, and 2740 indicate low, moderate, and high perceived stress, respectively.

##### Other data collected

Additional data will be collected about the following items:
Socioeconomic status (annual income, and educational and occupational levels)Smoking statusFamily meals per weekFamily PA per weekFamily postal addressNumber of years parents and children have been living in SpainHousehold characteristicsC.**Data collection for educators and CCC**

We will collect data on CCC characteristics, such as: (i) location; (ii) total number and ages of children, and family workshop and sport educational sessions attendance; (iii) number of people of the staff; and (iv) if applicable, number and characteristics of health promotion actions implemented in the CCC. The latter will be collected at the beginning of the project. Moreover, we will also collect CCC staff data on the following parameters: (i) socio demographic characteristics; (ii) educational level and studies; and (iii) grade of motivation and awareness through healthy lifestyle promotion, at the beginning and at the end of each edition.

### Evaluation plan

We will collect all data for each edition at baseline and 10months after the intervention (post-evaluation). Moreover, a follow up evaluation will be performed in the intervention group 12months after the post-evaluation, to study whether the impact of FIVALIN is sustained in the long term. After the assessment sessions, each participating family from the intervention and control groups will receive an incentive (e.g., a reusable water bottle, a technical shirt, or a ball).

The intervention fidelity and process evaluation indicators will be assessed in different ways, such as: i) periodical project coordinators meetings; ii) follow-up meetings and evaluation sessions with CCC educators; iii) voice audios after project activities recorded by GF educators; iv) registration of family attendance and level of satisfaction after each workshop; and v) a qualitative assessment at the end of each project edition (focus groups and interviews to key stakeholders). The evidence derived from the previous assessment activities will be used with 2 aims, such as: (i) improve the project management after each edition; and (ii) incorporate future improvements to the project basis, once the three editions will be implemented and the final data of the present study will be gathered. The project methodology, activities, assessment tools, staff profile, and the expected outcome will be the same for the 3 editions because a final evaluation of pooled data will be performed.

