## Methods

### Study design

To determine the effects of the FIVALIN project, we will perform a quasi-experimental design with a control group.

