### Subjects

The study will involve low SES children aged 812years and their families from 60 Community Child Centers (CCC) in the metropolitan area of Barcelona. A CCC is a childcare center that promotes the education of children from low income families by providing them academic support and emotional education after school. A total of 810 children and 600 parents will be included in the intervention groups, and likewise for the control groups. These population samples will be distributed among three consecutive editions of the FIVALIN project (20192020, 20202021, and 20212022), and will include at least one adult and one child per low-income family. A total of 30 CCC (15 in the intervention group and 15 as controls) will be involved per edition. CCC from control group will be invited to be part of intervention group on the subsequent edition, and15 new CCC will be recruited in the control groups of the second and third editions. In total, after the three edition, 60 CCC will be enrolled in the project (see Table1). It is not expected that CCC participating in the intervention group during first or second edition will continue providing the intervention in subsequent editions. 18 socioeconomic vulnerable children (8- to 12-year-old) and their families will participate per CCC. Therefore, considering the intervention and control groups, we expect a total participation of 540 children and 400 adults per edition. Participants will be recruited by CCC, by inviting families that are already participating in their activities. They receive communicative material (flyers and leaflets) to introduce the project and motivate them to participate. For convenience, recruitment and allocation will be conducted by Gasol Foundation (GF), considering the characteristics of the CCC: activities, number of educators, parents involvement, etc.

**Table 1 Tab1:** Number of CCC per FIVALIN edition

CCC from the	1st edition	2nd edition	3rd edition
Intervention group	1 to 15 CCC *(new)*	CCC from the control group of the 1 edition 16 to 30 CCC	CCC from the control group of the 2 edition 31 to 45 CCC
Control group	16 to 30 CCC *(new)*	31 to 45 CCC *(new)*	46 to 60 CCC *(new)*

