### Sample size calculation

We estimate that it will be necessary to include 270 children and their parents, both in the intervention and control groups, per edition of the FIVALIN project. We expect a statistically significant decrease in body mass index (BMI) z-score of 0.15 in the intervention group, in comparison to the control group. From the PRE to POST evaluations, for each of the three editions. Previous community intervention [35] that aimed to prevent childhood obesity through the promotion of healthy lifestyles, and were carried out in the same geographical context and among children of the same ages. They showed a mean zBMI reduction of 0.10. The FIVALIN project is a more intense intervention and, for this reason, we expect a higher zBMI reduction.

We assume a 0.05 alpha risk, a 0.2 beta risk in a bilateral contrast, and 20% loss to follow-up. We expect to recruit significantly less families with 2 children in the age range of 8 to 12years, than families with one child. Therefore, we performed a simplified approximation of the sample size by counting only for one outcome (zBMI of one child). The sample size was calculated using the online sample size and power calculator GRANMO (IMIM-Spain).

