### Intervention

The FIVALIN project is an FBI addressed to school age children (8- to 12-year-old) and their parents/caregivers. It has been created to be part of a Multi-Level Multi Component (MLMC) intervention that pretends to prevent childhood obesity from early ages, and along all the developmental stages, until adulthood. The pre-adolescence stage is a key period to sustain the healthy lifestyles promotion activities to prevent a deterioration at subsequent stages.

The FIVALIN project will be developed in three editions (1st 2019/2020; 2nd 2020/2021; 3rd - 2021/2022) of 10months each. The plan will be coordinated by the multidisciplinary health team of the GF, supported by educators of the CCC and a trained team of volunteers. We expect that the GF team will be stable. To ensure intervention consistency, we will activate different strategies (see Additionalfile1). Volunteers will be recruited by GF. They will contact the entity and, after a welcoming training, they will be involved in the project activities.

The study will be conducted after school time in CCC in the metropolitan area of Barcelona. In CCC, parents are encouraged to be part of their childrens education. For the intervention group, we define two modalities of participation (low and high), depending on the project intensity. The main difference between the two modalities is that children participating in the high intensity modality will do an extra activity, attending 32 sports educational sessions implemented by CCC educators. Each CCC will choose the modality that best fits their internal organization (see Table2 and Figs.1, 2 and 3)*.* Additionally, educational material, mobile messages, and videos will be sent to families in order to reinforce the health behaviors promoted during the workshops and sport educational sessions. Moreover, mobile messages will remind workshops date and hour to promote the participants attendance. CCC participating in the control group will be invited to be part of the intervention group in the next edition. The control group will receive the usual care provided in the CCC program plus a pre-evaluation and post-evaluation session. Moreover, they will receive a family workshop aimed to generate healthy lifestyle awareness and engagement, in order to reduce shortcomings in the post-evaluation.

**Table 2 Tab2:** FIVALIN project activities description by participation options

Activity description	Intervention		Control
	High intensity	Low Intensity	

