## Discussion

The epidemic of overweight and obesity presents a major worldwide challenge for chronic disease avoidance and health throughout life. Preventing overweight in children may have the greatest long-term effects [51]. Pediatric obesity is more common in population groups with a lower SES [20]; therefore, strategies and programs need to prioritize the inclusion of vulnerable groups [52]. The FIVALIN project is an FBI that uses a novel approach to prevent overweight among children through promoting healthy lifestyles. The plan targets low-SES families and is implemented via CCC.

A major strength of this project is that we will be able to carry out a follow-up 12months after the post-evaluation. Another strength is the multiple behavioral approach. A systematic review revealed gaps in the behavioral domains targeted in childhood obesity prevention, with only 16% of the analyzed intervention directed at four behavioral domains (PA, Nutrition, Media use, and Sleep) [31]. However, it is important to target and evaluate all the behavioral domains that influence weight status. Indeed, FBI studies measuring secondary outcomes have found significant changes in two or more behavioral aspects [29].

Although the internal features of the CCC prevent us from conducting a properly randomized trial, the socio-demographic characteristics of the intervention and control groups of the first edition of FIVALIN are similar. It could be argued that, since lifestyle variables will be measured by self-administered questionnaires, the participants` low level of education may influence their ability to understand and answer them. Nevertheless, families with the lowest reading and comprehension skills will receive the support of trained researchers to complete the questionnaires, and biases are expected to be similar in the intervention and control group.

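### The 12-month follow-up is planned in the intervention group only, so it can describe whether the level at post-evaluation is held but not whether the effect against control is sustained

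*Protocol article*

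**What the plan says.** All places are in the protocol article.

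- **Evaluation plan.** Data are collected in every edition at two times: "We will collect all data for each edition at baseline and 10months after the intervention (post-evaluation". A third time is then added for one group, with its purpose: "a follow up evaluation will be performed in the intervention group 12months after the post-evaluation, to study whether the impact of FIVALIN is sustained".
- **Intervention.** The control group's measurements are limited to two sessions: "The control group will receive the usual care provided in the CCC program plus a pre-evaluation and post-evaluation session".
- **Study design and Sample size calculation.** The design is stated as "we will perform a quasi-experimental design with a control group", and the expected effect as "We expect a statistically significant decrease in body mass index (BMI) z-score of 0.15 in the intervention group, in comparison to the control group".
- **Statistics.** Significance is judged on differences between the intervention and control groups.
- **Subjects and Table 1.** "CCC from control group will be invited to be part of intervention group on the subsequent edition". In Table 1 the edition 2 intervention row reads "CCC from the control group of the 1 edition 16 to 30 CCC", and the edition 3 row moves centres 31 to 45 across in the same way.
- **Discussion.** "A major strength of this project is that we will be able to carry out a follow-up 12months after the post-evaluation". The limitations discussed there are self-selection, educator motivation, parent engagement, self-report, fidelity assessment and non-random assignment. The absence of a comparator at 12 months is not among them.

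**The concern.** The stated purpose of the follow-up is about the programme's impact, and everywhere else the plan sets out its effect as a contrast with control. At 12 months only one side of that contrast is observed. A change, or no change, in the intervention group after post-evaluation combines what remains of the effect with whatever would have happened anyway: calendar trend, ageing, and which families return for a third assessment.

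This matters more in a prevention programme than in a treatment trial. The benefit may consist of treated children holding steady while untreated children drift upward, so a flat line in the treated group is hard to interpret alone. At stake is a report that the effect was sustained, or was lost, on data that cannot show either. The pre-to-post comparison is not at stake.

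**Working it through.** **Step 1: who is measured when.**

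| Time | Intervention | Control | Source |
|---|---|---|---|
| Baseline | yes | yes | Evaluation plan; Intervention |
| Post-evaluation (POST) | yes | yes | Evaluation plan; Intervention |
| POST + 12 months | yes | not planned | Evaluation plan |

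**Step 2: what a between-group statement at 12 months needs.** Write E for the effect (intervention minus control), and cI and cC for the mean changes from POST to 12 months in the intervention group and in comparable untreated children. Then

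E(12 months) = E(POST) + cI − cC.

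E(POST) is estimated from both groups and cI from the follow-up. The term cC is not measured in any edition.

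**Step 3: why the missing term decides the answer.** Take the planned effect, E(POST) = −0.15, and suppose that the intervention group is flat afterwards, cI = 0. Then E(12 months) = −0.15 − cC. The three values of cC below are assumptions, set at zero and at plus or minus the planned effect only to show the logic. The documents give no figure for cC, and these values are not forecasts.

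- cC = −0.15: −0.15 + 0.15 = 0 (effect gone)
- cC = 0: −0.15 (effect held)
- cC = +0.15: −0.15 − 0.15 = −0.30 (effect doubled)

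The same intervention-group data fit all three. More children would estimate cI more precisely and leave cC unknown.

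**Step 4: can the original controls supply cC?** By plan, centres 16 to 30 (edition 1 controls) and 31 to 45 (edition 2 controls) enter the intervention in the following edition, that is, during the follow-up year. They are invited, so this is planned and not certain. For the edition 3 controls, centres 46 to 60, Table 1 shows no later edition, but no 12-month measurement is planned for them either. As planned, then, no edition has a concurrent control measurement at 12 months.

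**Step 5: can the next edition's new controls stand in?** For editions 1 and 2, the follow-up year runs alongside editions 2 and 3, which recruit new control centres measured before and after. Their change is the nearest available figure to cC, with clear limits:

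- An edition lasts 10 months and the follow-up interval is 12, so 12 − 10 = 2 months are not covered.
- The overlap presumes that POST falls at the end of an edition. The Evaluation plan literally places it 10 months after the intervention, and on that reading the windows no longer match.
- The centres are different ones, assigned by convenience.
- They receive a family workshop and educational material, so they are not wholly untreated.
- Their children enter at 8 to 12 years, whereas the followed-up children start this interval about 10 months after their own entry.

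This can give context. It cannot replace cC.

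**The case against.** The strongest reply is that the Evaluation plan does not define impact. The 0.15 is a sample-size assumption tied to the pre-to-post period, and the follow-up sentence can be read as asking only whether the level reached at POST is held. One group can describe that. Offering control centres the programme in the next edition is also a deliberate and reasonable choice, and a one-group follow-up is its natural consequence. Both points stand. They support keeping the follow-up under a purpose that it can meet; they do not make a within-group change into evidence about the effect against control.

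Several stronger readings are tempting, and the documents do not support them.

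- **That the planned two-group model breaks down at 12 months.** Statistics never assigns the generalized estimating equation model to the follow-up. How those data would be analysed is left open in this article, and that is not an error.
- **That the Discussion claims a demonstrated lasting effect.** It praises being able to carry out a follow-up and claims no controlled result.
- **That a size can be put on the bias.** The documents give no figure for change in untreated children after POST.
- **That regression to the mean is a main threat.** There is no weight-based entry criterion. The Discussion mentions only that parents concerned about weight or health behaviour may be more likely to join.
- **That ageing is wholly uncontrolled.** A BMI z-score outcome handles age in part.

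An analysis plan not shown here could settle wording and methods, but it cannot analyse control data that the plan does not collect.

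**Conclusion.** The point holds in a limited form. As written, the 12-month follow-up can describe whether the intervention group keeps the level reached at POST. It cannot support a between-group conclusion that the effect is sustained or lost, because the untreated change over the same interval is not measured and calendar trend, ageing and selective return cannot be separated from the effect. A reader might infer that the follow-up is worthless or that no conclusion from it could stand. That goes too far, since a within-group description remains valid and useful.

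No numerical size can be attached; the calculation above only shows that the missing term determines the answer. The conclusion rests on two readings: that impact means the effect the plan sets out elsewhere, against control, and that control children are measured twice and not again as controls. The correction is worth making because a stated purpose and a headline strength depend on it. It leaves the pre-to-post comparison untouched.

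**What to change.** 1. **Evaluation plan:** restate the purpose of the 12-month evaluation as a descriptive within-group change from POST to 12 months in the intervention group.
2. **Discussion, strengths:** qualify the follow-up as a strength for describing within-group maintenance.
3. **Discussion, limitations:** add that, as planned, no edition has a concurrent control measurement at 12 months, so change in the intervention group cannot be separated from change that would have occurred without the programme.
4. **Optional, editions 1 and 2:** show the pre-to-post BMI z-score change of the next edition's new control centres beside the follow-up change. Label it as supportive context only, and state that it covers about 10 months against 12, comes from different non-randomised centres that receive a workshop, and involves somewhat younger children.

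Items 1 to 3 cost a few sentences and make the long-term claim weaker. Item 4 is one extra analysis of data already planned. A 12-month measurement of edition 3 controls would be new data collection, would help only if those centres stayed outside the programme, and is not needed for this correction.
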